### Laboratory procedures

#### PainCELL sample analysis

Venous blood collected in EDTA-coated vacutainer tubes and the synovial fluid collected in sodium citrate-coated tubes/sterile containers for the painCELL test will immediately be inverted several times to prevent blood from clotting. For the PBMC and SFMC isolation success to be maximised, the blood and synovial fluid will be cooled to room temperature before the cell isolation procedures initiate (30–60 min, depending on the ambient temperature). PBMCs are isolated using Optiprep density medium (Sigma-Aldrich #D1556; Castle Hill, NSW, Australia) as directed by the manufacturer using the mixer flotation method, as previously described.^23 26 27^ Due to the expected considerably small amount of synovial fluid available from sampling, this last step using Optiprep will not be performed for the SFMCs.

Isolated PBMCs and all SFMCs are diluted to 10^6^ cells/mL in enriched Roswell Park Memorial Institute Medium (RPMI) 1640 (10% fetal bovine serum, 2 mM l-glutamine and 1% penicillin/streptomycin) and plated into 96 well plates (100 µL per well). Various concentrations of innate immune stimulants will be added into the wells which include a TLR-2 agonist (Pam3; Merck #506350; Darmstadt, Germany; from 12.5 pg/mL to 1 mg/mL), and a TLR-4 agonist (LPS; InvivoGen #TLRL-3PELPS; San Diego, California, USA; from 12.5 pg/mL to 10 mg/mL) in a final volume of 200 mL/well. Plates are then incubated for 24 hours, following which 150 mL of the supernatant will be removed, transferred to a separate 96 well plate and stored at −80°C for later analysis. Supernatants are analysed using a Human Interleukin 1 eta (IL-1β) OptEIA ELISA Set II (BD Biosciences #557953; San Jose, California, USA) per the manufacturer’s instructions. The standard curve range for this assay is estimated to be 3.9–500 pg/mL. Supernatants are added to the ELISA either neat or diluted 1:10 to ensure the quantified values fall within the limits of the standard curve.

#### PainHS sample analysis

Venous blood samples collected in EDTA-coated vacutainer tubes and the synovial fluid collected in sodium citrate-coated tubes/sterile containers for the painHS test were frozen and stored at −80°C for later analysis. On the day of analysis, samples will be thawed in a 37°C water bath for 45 mins. The blood and synovial fluid will be washed with equal volumes of RPMI1640, centrifuged (240×g for 5 min) with supernatant removed and resuspended in 3–5 mL of RPMI. Cells of the blood and synovial fluid samples are counted and then placed on the imaging slides for HS imaging. An adapted fluorescence microscope (Olympus iX71) will be used with a 40×water U12 series objective (with wide transmission in UV range). LEDs with excitation wavelength bands centred at 334, 365, 385, 395, 405, 415, 425, 435, 455, 475, 495 nm, each about 10 nm wide produce close to monochromatic light to excite the sample’s auto-fluorescence. The corresponding sample emission will be measured with three epifluorescence filter cubes with the emission bands centred at 447 nm (60 nm wide), 587 nm (35 nm wide) and 700 nm long pass. Overall, in this work we use 18 spectral channels (ref) with the same channel numbering as used here,^40^ and each field of view will be imaged in all these 18 channels forming a HS image. Images are captured by a digital camera C1140, OCRA Flash 4.0 (Hamamatsu). Images will then be saved and digitally transferred for digital analysis by the Neuroimmunopharmacology laboratory.

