**Methods and analysis:**

This is a protocol for a prospective cross-sectional matched-subject observational study. We will include 20 adults undergoing unilateral primary TKA for painful advanced knee osteoarthritis, their contralateral pain-free knees as internal controls and 20 age and sex matched healthy controls without joint pain or functional limitation. All participants will undergo standardised clinical assessment and complete pain and psychological PROMs. In patients with TKA, venous blood will be collected pre-operatively. During TKA surgery, synovial fluid will be aspirated from the painful operated knee and the contralateral pain-free knee. Healthy controls will provide a single venous blood sample at a hospital visit. Peripheral blood mononuclear cells and synovial fluid mononuclear cells will be stimulated ex vivo with toll-like receptor 2 and 4 agonists to quantify IL-1β release. In parallel, hyperspectral imaging will characterise unstimulated immune cell phenotypes. Multivariable statistical and machine-learning approaches will relate biomarker profiles to pain and psychological PROMs.

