Secondary exploratory aims include (1) assessing associations between immune responses (IL-1β expression) and subjective pain scores, (2) exploring relationships between immune responses and psychological factors (anxiety, depression, pain catastrophising) and (3) evaluating HS imaging as a complementary approach for characterising immune cell phenotypes by assessing the relationship between HS imaging hues and IL-1β expression.

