### Sample collection

Preoperatively, at the pre-admission clinic 2–4 weeks before surgery, enrolled TKA-awaiting patients (n=20) will receive routine venous blood sampling for elective surgery preparations at Noarlunga Hospital. At that same blood collection moment, a total of 30 mL of blood will be collected for this study: 10 mL for the functional immune stimulation assay used to quantify cytokine release (IL-1β) (ie, ‘painCELL test’), 10 mL for the HS imaging-based analysis of immune cells used to characterise cellular autofluorescence signatures and identify potential phenotypic differences between participant groups (ie, ‘painHS test’) and 10 mL for storage and backup in case of experimental assay complications. Also, all preoperative questionnaires (HADS, PCS and NRS-pain) will be completed during this visit.

Subsequently, perioperatively during the elective TKA surgery, synovial fluid will be collected from the painful knee receiving TKA surgery, just after opening the knee joint. A total of 30 mL of synovial fluid will be collected for this study: 10 mL for the painCELL test, 10 mL for the painHS test and 10 mL for storage and backup in case of experimental assay complications.

Similarly, the contralateral pain-free knee will be punctured for 5–30 mL synovial fluid directly after surgery when the patient is still under narcosis, so that the patient will experience no additional discomfort. This procedure is included to enable within-subject comparison between painful osteoarthritic and pain-free joints within the same patient, thereby reducing inter-individual variability in immune response measurements. The aspiration will be performed under sterile operating theatre conditions by an experienced orthopaedic surgeon, following standard aseptic procedures to minimise the risk of complications such as infection.

All healthy blood-control individuals without pain symptoms in both knees (n=20) will attend Flinders Medical Centre or Noarlunga Hospital, where similarly venous blood samples will be collected for the study, which includes 30 mL of blood in total: 10 mL for the painCELL test, 10 mL for the painHS test and 10 mL for storage and backup in case of experimental assay complications.

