#### Secondary outcome analysis: painHS data

HS images are pre-processed as previously described.^41^ This will be followed by cell segmentation, carried out in an automatic approach using a parametric watershed algorithm with a partial set principal components (PCA) image. The channels employed in the PCA segmentation image are found through trial and test. This segmentation protocol will be augmented with additional manual segmentation using the phase contrast image and selecting cells at random. By estimation, this will yield 70–90 cells from each image, belonging to one of the following four sample groups: (1) blood samples from painful symptomatic osteoarthritis patients (participant group 1), (2) synovial fluid samples from painful symptomatic osteoarthritis patients (participant group 1), (3) synovial fluid samples from contralateral pain-free control knee (participant group 1) and (4) blood samples from pain-free controls (participant group 2).

After each cell is segmented from the background, a number of quantitative features are calculated using the segmented cells to parameterise the cell data, with the primary goal of delineating participant population membership. In particular, for each cell we will calculate ratios of mean channel intensities of pairs, correlation of channel pixel intensities and coherence of the statistics of the channel pairs. The feature data for all cells will then undergo a singular value decomposition as described previously.^40^ These uncorrelated variables are then further used for supervised discriminatory analysis.^40 41^ The LDA will provide another set of seven feature variables maximising the separation between the sample populations.^40^ These are then optimally projected by using the second linear discriminant analysis onto two dimensions to obtain a graphical representation, showing the optimal participant group separation. Subsequently, they are projected again using LDA on a single optimised dimension. Receiver operator curves will be plotted to assess the sensitivity and specificity of the approach.

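### The painHS procedure states no step that separates, preserves or identifies immune cells, so it does not show that the cells imaged are the immune cells it is meant to characterise

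*Protocol article*

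**What the plan says.** **Target.** The abstract says that "hyperspectral imaging will characterise unstimulated immune cell phenotypes". Sample collection assigns "10 mL for the HS imaging-based analysis of immune cells used to characterise cellular autofluorescence signatures". The third secondary aim, under Aim, design and setting of the study, is "evaluating HS imaging as a complementary approach for characterising immune cell phenotypes by assessing the relationship between HS imaging hues and IL-1β expression".

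**Handling.** PainHS sample analysis starts from EDTA blood tubes and citrate-coated tubes or sterile containers of synovial fluid, which "for the painHS test were frozen and stored at −80°C for later analysis". When imaging is due, the protocol specifies that "samples will be thawed in a 37°C water bath for 45 mins". The fluids are then "washed with equal volumes of RPMI1640, centrifuged (240×g for 5 min) with supernatant removed and resuspended in 3–5 mL of RPMI". After that, "Cells of the blood and synovial fluid samples are counted and then placed on the imaging slides for HS imaging".

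**Selection of cells.** Secondary outcome analysis: painHS data uses an automatic watershed segmentation, "augmented with additional manual segmentation using the phase contrast image and selecting cells at random". It expects 70–90 cells per image.

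**Contrast with painCELL.** PainCELL sample analysis isolates mononuclear cells from the blood tube with OptiPrep density medium. It says openly that this step is skipped for synovial fluid because little fluid is expected.

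**The concern.** The stated target is immune cells, but nothing in the printed procedure selects them. Unfractionated blood consists overwhelmingly of red cells. A method that images all cells left after thawing, and then segments them without a cell-type rule, may therefore be looking mostly at something else. Freezing adds a second problem: without stated protection or a viability check, it is unknown what condition the leucocytes are in when imaged.

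Two consequences follow for the analysis. First, the discriminant analysis is built to maximise separation between sample groups. It will use any systematic difference in cell composition or freeze-thaw damage, whether or not that difference relates to pain, and a good ROC curve would not reveal the cause. Second, the third secondary aim relates the imaging to IL-1β. For blood, that IL-1β comes from isolated PBMCs, which are not the cell population described for imaging.

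**Working it through.** **Step 1: the procedures side by side.**

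| Step | painCELL, blood | painCELL, synovial fluid | painHS, both fluids |
|---|---|---|---|
| Cell separation | OptiPrep isolation | Explicitly omitted | None stated |
| Red-cell removal | Through the isolation step | None stated | None stated |
| Cells frozen | No (supernatant is frozen after 24 h stimulation) | No (same) | Yes, sample frozen at −80°C |
| Freezing medium | Not applicable | Not applicable | None stated |
| Post-thaw viability or cell-type check | Not applicable | Not applicable | None stated |
| Rule restricting analysis to immune cells | Isolation itself | None stated | None stated |

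The gap in the last column is real for both fluids. The mismatch with isolated PBMCs applies to blood only, because painCELL does not density-separate synovial cells either.

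**Step 2: what this could mean for blood.** The plan gives no figure for the leucocyte share, so there is nothing to reproduce. The following is an illustration.

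Inputs:
- From the protocol: 70–90 cells per image; midpoint 80 used.
- Assumed, not in the document: red cells R = 4–5×10^6/µL; leucocytes W = 5–10×10^3/µL.
- Unknown, so varied: sR and sW, the fractions of red cells and leucocytes still present as segmentable cells at imaging.
- Assumed: segmented cells are a random draw from all cells on the slide.

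Formula: leucocyte share = W·sW / (W·sW + R·sR); expected leucocytes among 80 cells = 80 × share.

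Equal survival (sR = sW):
- Low: 5,000 / (5,000 + 5,000,000) = 0.10%; 80 × 0.00100 = 0.08.
- High: 10,000 / (10,000 + 4,000,000) = 0.25%; 80 × 0.00249 = 0.20.

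That is one leucocyte in roughly every 5 (1/0.20) to 12.5 (1/0.08) images.

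Unequal survival:

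| sR | sW | Low | High | Leucocytes per 80 cells |
|---|---|---|---|---|
| 10% | 100% | 5,000/505,000 = 1.0% | 10,000/410,000 = 2.4% | 0.8–2.0 |
| 1% | 100% | 5,000/55,000 = 9.1% | 10,000/50,000 = 20% | 7.3–16 |
| 0.1% | 100% | 5,000/10,000 = 50% | 10,000/14,000 = 71% | 40–57 |
| 0.1% | 10% | 500/5,500 = 9.1% | 1,000/5,000 = 20% | 7.3–16 |

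Leucocytes are a majority only if W·sW > R·sR, that is sR/sW < W/R. This threshold is 5,000/5,000,000 = 0.1% at one end and 10,000/4,000,000 = 0.25% at the other. Red cells would have to survive at less than about one four-hundredth to one thousandth of the leucocyte rate.

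**Step 3: synovial fluid.** The document gives no red-cell content for synovial fluid, so Step 2 cannot be applied to it.

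**The case against.** The strongest reply is that this is a condensed article. Silence about a cryoprotectant does not mean that none is used, and bench detail may sit in the full protocol or in the cited methods. That stands for the freezing medium. It is less persuasive for separation. The painHS section gives thaw time, spin force, wash ratio, resuspension volume and excitation bands, and it refers throughout to blood and synovial fluid, never to PBMCs or SFMCs. The painCELL section next to it states isolation and even says where it is omitted. The citations in the painHS analysis section are attached to image pre-processing and feature analysis, not to specimen handling.

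A second reply is that the result depends entirely on differential survival. This is correct: under the assumptions above, the leucocyte share runs from 0.1% to 71%. A reader might infer that the test images red cells, ghosts and debris instead of immune cells, so that the third secondary aim cannot be answered. The documents do not support that. They do not say which cells survive the thaw, and the low figures hold only with near-equal survival. The removed supernatant would also carry off at least part of any free haemoglobin.

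Third, all samples of a given fluid follow one printed procedure, so handling alone need not differ between the groups compared. That is fair, and the bias is therefore a possibility and not a demonstrated effect. A shared procedure still does not make the imaged cells the intended ones.

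**Conclusion.** The point holds as a mismatch between stated target and stated method. As printed, the painHS procedure contains no step that separates, preserves or identifies immune cells, so it does not show that it measures immune-cell phenotype.

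For blood the possible size is large: about 0.1–0.25% leucocytes, or 0.08–0.20 per 80 segmented cells, if red and white cells survive equally. This rests on assumed counts and on random selection of cells. The share improves only with strongly selective red-cell loss, which the plan neither states nor checks. Group separation on imaging could therefore reflect red-cell content or freeze-thaw damage. For synovial fluid, only the lack of stated preservation and identification can be raised.

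The Data analysis plan labels all secondary analyses exploratory, and the primary EC50 comparison is unaffected. The matter is still worth settling now: Ethics and dissemination states that sample collection has not begun, and cells damaged in storage cannot be recovered later.

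**What to change.** In PainHS sample analysis:
- Run the painHS blood tube through the OptiPrep isolation already used for painCELL before freezing, or image the isolated cells fresh.
- If freezing, store isolated blood cells and spun-down synovial cells in a cryoprotective medium, handled identically for the two knees. A simple spin avoids the density step that painCELL drops because of small synovial volumes.
- Record post-thaw viability.

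In Secondary outcome analysis: painHS data, restrict both automatic and manual segmentation to intact nucleated cells.

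If these steps are already in the working procedure, it is enough to correct the painHS section to state them and to reconcile it with Sample collection and the painHS analysis section.

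The cost is some extra same-day bench time, freezing medium and a viability count. The laboratory already processes a painCELL tube from the same participants by the same isolation method. No extra participants, visits or blood are needed.

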### Sample size calculation

A sample size calculation based on achieving 90% power and a Type 1 error rate of 5% was chosen. The calculation was based on primary analyses and determined that 24 participants in total (12 participants per group) would be required to detect a 2.40 difference in the Least Squares means for EC50 (concentration-response parameter: concentration which produces 50% of the maximal effect, to determine the responsiveness of PBMC and SFMC to LPS and PAM3 stimulation) assuming a within-group SD of 1.78. The clinically significant difference in EC50 was estimated based on parameters described by Evans *et al*.^29^ To account for a potential 10% loss to follow-up and safety margin with regards to sample analyses, a total sample of 40 participants (20 per group) is to be recruited.

It should be noted that the calculated sample size was based on the primary analysis and may not provide sufficient statistical power for all planned secondary analyses, such as investigating associations between immune responsiveness (PBMCs and SFMCs responses) and psychological symptoms including anxiety, depression or pain catastrophising. General statistical guidance for multivariable modelling recommends an adequate number of observations per covariate to ensure model stability (eg, 10 patients per use of 1 covariate). Therefore, the number of covariates included in secondary analyses will be kept limited (only one psychological variable per model) to maintain analytical feasibility. As these secondary analyses are exploratory in nature, their findings will be interpreted accordingly. The present study represents an initial exploratory investigation of neuroimmune pain biomarkers within an orthopaedic population.

### Data analysis plan

Primary analyses aim to assess whether peripheral immune response parameters differ between painful osteoarthritic knees and pain-free controls. This will be evaluated using both within-subject comparisons (painful knee vs contralateral pain-free knee in patients undergoing TKA for synovial fluid analyses) and between-group comparisons (patients vs healthy controls for peripheral blood analyses). Secondary analyses will explore associations between immune response parameters and PROMs for pain intensity and psychological factors including anxiety, depression and pain catastrophising. All secondary analyses, including multivariable and machine-learning approaches, are exploratory in nature and aimed at hypothesis generation rather than confirmatory inference.

#### Primary outcome analysis: painCELL data

Concentration-response curves from the in vitro innate immune stimulated IL-1β release from PBMCs and SFMCs are calculated using GraphPad Prism version 8 (MathWorks; Natick, Massachusetts, USA). Differences between pain-free controls and painful symptomatic osteoarthritis patients (within the same patient for synovial fluid samples and a different patient for blood samples) will be assessed on EC_50_, Hillslope and ‘Top’ (or E_max_). The ‘Bottom’ value will be constrained to a constant of 0. An F-test in GraphPad Prism will be performed to determine if these values should be the same or different between the participant groups. The goodness of fit obtained from the TLR-2 stimulation is not sufficient to warrant presentation in the results, owing to lower-than-expected cytokine expression in the assays.

The painCELL assay cytokine data will be combined with osteoarthritis severity and NRS-pain reports, as well as other demographics (such as mental state) for each participant in a data file. Additional parameterisation of the data set will be performed to capture the delta change in cytokine release between low and high concentration innate immune challenges and between these delta values and the steepness of the concentration response.

First, a feature selection (dimensionality reduction) step will be performed to remove highly correlated variables, by examining the correlation matrix and applying the ‘Bivariate Correlations’ function to identify and exclude variables with Pearson Correlation coefficients greater than 0.8. For each specific hypothesis test, data subsets will be created using the ‘Select Cases’ function to exclude irrelevant subject data (eg, when testing the model for Healthy synovial sample Controls and the contralateral painful knee, Healthy blood sample Controls data will be excluded).

For analysis, a randomised approach with at least a 20% holdout validation and test dataset will be employed. The dataset will be split to ensure that the test dataset is not included in the model training phase. For the categorical selection hypotheses, several classification techniques will be applied in parallel, expected to include: Linear Discriminant Analysis (LDA), Classification and Regression Trees, K-Nearest Neighbours, Support Vector Machine and Random Forest models. The best-performing model will be identified based on the highest accuracy and lowest error rate, for which a confusion matrix will then be created.

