The primary aim of this exploratory study is to investigate whether peripheral immune responses, IL-1β expression quantified from both peripheral blood mononuclear cells (PBMCs) and synovial fluid mononuclear cells (SFMCs), differ between patients with symptomatic knee osteoarthritis awaiting TKA and pain-free healthy controls. We hypothesise that stimulated immune responses (IL-1β release) are elevated in patients with symptomatic knee osteoarthritis compared with pain-free controls. Secondary exploratory analyses will (1) examine associations between immune responses, subjective pain measures and psychological factors and (2) evaluate hyperspectral (HS) imaging as a complementary approach for characterising immune cell phenotypes.^32^ This study is intended as a hypothesis-generating study to inform future research on objective pain biomarkers in orthopaedic populations, and to address the absence of objective, biologically anchored pain measurement in orthopaedic surgery. This exploratory study applies neuroimmune biomarker technology to musculoskeletal pain, and may provide a foundation for integrating objective biological markers with subjective pain assessment to improve clinical decision-making and ultimately contribute to a more multidimensional approach of pain assessment.

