### Clinical assessment and questionnaires

The primary outcome included EC50 (concentration-response parameter: concentration which produces 50% of the maximal effect) for IL-1β release, to determine the responsiveness of PBMC and SFMC to LPS and PAM3 stimulation. Osteoarthritis severity of the painful knee will be graded by an orthopaedic surgeon based on Kellgren-Lawrence and self-assessed pain scores will be determined by the patient preoperatively for both knees using the NRS-pain scores. Additionally, preoperative mental state will be assessed by completing two Patient Reported Outcome Measures (PROM): the Hospital Anxiety and Depression Scale (HADS) questionnaire,^34^ and the Pain Catastrophizing Scale (PCS) questionnaire.^35 36^ The HADS consists of an anxiety (HADS-A) and a depression (HADS-D) subscale, each including seven items scoring 0–3, resulting in a total maximum score of 21 per subscale. Scores of 8–11 are considered borderline anxiety or depression, whereas scores>11 are considered presumable anxiety or depression.^37^ In this study, an HADS-A or HADS-D score ≥8 will be categorised as the presence of anxiety or depression, respectively.^34 38^ The PCS is a validated questionnaire consisting of 13 statements regarding feelings and thoughts during experiencing pain.^35 36^ Patients rate these statements on a 5-point Likert scale ranging from ‘not at all’ to ‘all the time’ with the total score ranging from 0 (no catastrophising) to 52 (severe catastrophising). A score of 30 or higher is considered clinically relevant catastrophising;^36 39^ as such, patients will be considered pain catastrophizing (PC) or non-PC patients.

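### The primary outcome is defined inconsistently: one EC50 comparison is powered, but several parameters and contrasts are analysed as primary, and EC50 does not directly express the hypothesis of elevated release

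*Protocol article*

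**What the plan says.** All references are to the Protocol article.

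- **Hypothesis (Introduction).** "We hypothesise that stimulated immune responses (IL-1β release) are elevated in patients with symptomatic knee osteoarthritis compared with pain-free controls". This is directional and about the amount released.
- **Named outcome (Clinical assessment and questionnaires).** "The primary outcome included EC50", explained there as the agonist concentration giving half the maximal response, for blood cells (PBMC) and synovial cells (SFMC) under both LPS and PAM3.
- **Sample size (Sample size calculation).** "A sample size calculation based on achieving 90% power and a Type 1 error rate of 5% was chosen". The result is that "24 participants in total (12 participants per group) would be required to detect a 2.40 difference in the Least Squares means for EC50", "assuming a within-group SD of 1.78". Recruitment is then set at 20 per group.
- **Contrasts (Data analysis plan).** Two contrasts serve the primary analysis: painful versus contralateral knee within patients for synovial fluid, and patients versus healthy controls for blood.
- **Parameters (Primary outcome analysis: painCELL data).** Differences "will be assessed on EC_50_, Hillslope and" Top (Emax), using an F-test "to determine if these values should be the same or different between the participant groups". The same section says that TLR-2 results will not be presented because the curve fit is inadequate.
- **Aims (Introduction; Aim, design and setting of the study).** Both set IL-1β from PBMC and SFMC against healthy controls. Under Sample collection, healthy controls give blood only.
- **Status.** The Introduction, the aims section and the end of the sample size section call the study exploratory, and the Introduction calls it hypothesis-generating.

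**The concern.** A 5% error rate and 90% power are properties of a particular test. Here they come from one two-group EC50 comparison, while the section headed as the primary analysis contains three curve parameters in two compartments and, depending on how the TLR-2 sentence is read, one or two agonists. Nothing says which of these decides the primary question. A favourable result on any of them could be presented as the primary finding, and readers could not tell which comparison the design figures describe.

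A second problem affects what is being asked. If painful samples release more IL-1β at every agonist concentration, but reach half-maximum at the same concentration, the hypothesis is true and the EC50 difference is zero. If the cells are more sensitive, EC50 falls. The document ties neither EC50 nor a direction of change in EC50 to the hypothesis.

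**Working it through.** **1. Reproducing the stated sample size.** Inputs from Sample size calculation: difference 2.40, SD 1.78, alpha 0.05, power 0.90. Sidedness is not stated; two-sided is assumed because the F-test asks whether values are the same or different.

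n per group = 2 × [SD × (z0.975 + z0.90) / difference]² = 2 × [1.78 × (1.960 + 1.282) / 2.40]² = 11.56, rounded up to 12, so 24 in total. The stated figure reproduces exactly, for **one** comparison of two independent groups. (The t distribution gives 13 per group, and 88.4% power at 12; this is immaterial with 20 planned. A one-sided normal calculation would give 10.) The 10% loss takes 24 to 24/0.9 = 26.7, so 27; the rest of the step to 40 is the unquantified safety margin.

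**2. Counting the primary tests.** The maximum is 3 parameters × 2 agonists × 2 contrasts = 12. The document also permits smaller counts.

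**3. Chance of at least one false positive.** With k independent tests, each at 5%, this is 1 − 0.95^k. The correlated columns come from a simulation with an assumed common correlation, since the document gives none.

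| Reading of the plan | k | Independent | Correlation 0.5 | Correlation 0.9 |
|---|---|---|---|---|
| EC50 only, LPS only | 2 | 9.8% | not run | not run |
| EC50 only with both agonists, or one global F-test per curve pair | 4 | 18.5% | 15.7% | 9.4% |
| Three parameters, TLR-2 not presented | 6 | 26.5% | 20.7% | 10.8% |
| Three parameters, both agonists | 12 | 46.0% | 31.9% | 13.5% |

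**4. EC50 against amount released.** Take release = Top × c / (c + EC50), slope 1, with illustrative values.

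| Concentration c | Top 100, EC50 10 | Top 300, EC50 10 | Top 100, EC50 1 |
|---|---|---|---|
| 1 | 9.1 | 27.3 | 50.0 |
| 10 | 50.0 | 150.0 | 90.9 |
| 1000 | 99.0 | 297.0 | 99.9 |

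Tripling Top triples release at every concentration and leaves EC50 unchanged. Lowering EC50 raises release at low and middle concentrations but hardly changes the maximum.

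**5. Power if one test is named.** Two-sample t-test, two-sided, noncentrality = 2.40 / [1.78 × √(2/n)]: 4.26 for n = 20 and 4.05 for n = 18 (20 less 10%).

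| Level | 18 per group | 20 per group |
|---|---|---|
| 0.05 (single test) | 97.5% | 98.6% |
| 0.025 (first Holm step for two tests) | 95.1% | 97.0% |

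These figures apply to the blood contrast only. Synovial power depends on the within-pair correlation, which is not given.

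**The case against.** The strongest reply is that the study is hypothesis-generating. The Introduction, the aims section and the sample size section all say so, and this covers the primary aim as well as the secondary ones. Strict familywise control is therefore not obligatory, and a level used to size one comparison is not a promise of control over all of them. That stands. What remains is that the sample size section attaches 5% and 90% to the primary analyses, and the Data analysis plan, where it contrasts exploratory work with confirmatory inference, mentions only the secondary analyses.

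The full analysis plan is not shown and may contain an adjustment or an order of testing. That also stands: the absence of an adjustment is not the finding. The finding is the visible disagreement between the sections that name, size and analyse the primary outcome.

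A reader might infer that the trial carries a 46% false-positive risk. The documents do not support that as a headline. It needs all twelve tests to count, independence between parameters fitted to the same curve, and inclusion of TLR-2 results that the plan says will not be presented.

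A reader might also infer that the EC50 mismatch inflates the error rate, or that higher release would go undetected. Neither follows. The mismatch affects which question is powered, not type I error, and Top is already among the parameters assessed.

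Finally, the comparison of SFMC with healthy controls in the aims is loose wording. The sample collection and analysis sections set out the workable contrasts, so no impossible analysis is planned.

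**Conclusion.** The point holds as an inconsistency in the primary definition. EC50 is named, one EC50 comparison is sized, and several parameters and contrasts are analysed as primary with no deciding test. Under the readings counted above, with independent tests each at 5%, the chance of some false-positive primary result is about 10% at the low end (two tests), 26% if TLR-2 is left out but all three parameters count, and 46% as a ceiling. Correlation reduces these; twelve tests at an assumed correlation of 0.9 give 13.5%. All these figures assume separate tests with no adjustment specified elsewhere.

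Separately, the powered parameter is potency while the hypothesis is about amount. This makes a primary result hard to interpret in either direction but leaves the error rate unchanged. The matter is worth correcting and cheap to correct; it does not undermine the planned number of participants.

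**What to change.** - **Name one primary test.** For example: EC50 for LPS-stimulated PBMC, patients versus healthy controls, two-sided at 5%, on whatever scale the 2.40 and 1.78 refer to. State that scale, which the document does not give. Say that the 5% and 90% apply to this test only.
- **Match the hypothesis to it.** Either reword the hypothesis as greater sensitivity, shown by a lower EC50, or make Top primary and redo the sample size for Top.
- **Label the rest.** The other parameters, PAM3 and the synovial contrast become secondary or exploratory. If the synovial LPS EC50 contrast is to stay co-primary, apply Holm across the two tests and state the within-pair correlation assumed for its power.
- **Correct the aims** in the Introduction and in the aims section, so that PBMC are compared with healthy controls and SFMC with the contralateral knee.

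If EC50 in blood is kept, the cost is wording, with no extra participants; choosing Top would need a new calculation. The document says recruitment has not begun, so the choice can still be prespecified. The price is that positive results on the other parameters can be reported only as secondary or exploratory.
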